## Abstract

**Background:**

China has the largest number of cases of diabetes with a high rate of uncontrolled blood sugar. Many studies show that family members’ involvement is related to better glycemic control. However, there is a significant problem with low participation of family members. The widespread use of WeChat provides an opportunity for family members to support their diabetic loved ones in their type 2 diabetes self-management practices. The main aim of this study is to examine the effectiveness of a family-based intervention via WeChat.

**Methods:**

A parallel, two-group, randomized controlled trial will be conducted in the central urban area of Jiading district in Shanghai, China. A total of 222 type 2 diabetics will be randomly divided into an intervention group or a control group using a 1:1 ratio. Patients in the intervention group will receive the usual care, and their family will get education in diabetes control and the importance of family support by subscribing to the WeChat public account. Both the patients and the family members will be followed up at 12 months after the intervention commences. Data collection is scheduled at baseline, 6-months, and 12-months.

**Discussion:**

Family involvement based on WeChat may generate ongoing support for type 2 diabetic patients and improve these patients’ health outcomes. A successful outcome of this study may also provide inspiration for other efforts to provide health education via WeChat.

**Trial registration:**

ChiCTR1900020736. Registered 15 January 2019.

**Electronic supplementary material:**

The online version of this article (10.1186/s12889-019-6702-8) contains supplementary material, which is available to authorized users.

## Background

Diabetes is a major contributor to cardiovascular diseases and a common cause of disability worldwide. Today nearly half a billion people are estimated to be living with the disease, although 50.0% remain undiagnosed [1]. In China, according to national surveys, the prevalence of diabetes has increased rapidly during the past few decades, from 0.9% in the 1980s to 10.9% today [2, 3]. The country has 121 million people with diabetes, which means one in four adults in China is a diabetic. Among these patients, however, only 36.5% have been diagnosed. The direct medical costs of diabetes is expected to be $47.2 billion in 2030 [4].

Glycemic control is one of the main objectives of treatment for diabetics since it is important for preventing and delaying diabetes-related complications. However, the 2013 national survey in China shows that only 39.7% of diagnosed patients were considered to have adequate glycemic control [3]. One possible reason may be poor adherence to diabetes self-management (DSM) behaviors and bad lifestyles among the patients with type 2 diabetes, especially among the elderly [5, 6].

Type 2 diabetes has been one of the leading non-communicable diseases in China. The Chinese Government launched a health management program for type 2 diabetes as a part of their national basic public health services in 2009 wherein diabetic patients could apply for registration in the health management system of their local health community centers. By the end of 2016, the number of registered diabetes patients had reached 27.81 million [7]. The National Guideline for Basic Public Health Services clearly state that the health community centers should provide services to diabetics such as blood glucose testing, physical examination, health education, and nutrition guidance [8]. Health education is considered to be a routine means to promote patients’ DSM. However, due to patients’ poor understanding and co-operation, the service is not effectively implemented, as shown by the failure to raise patients’ awareness of the necessity of glycemic control and to improve their lifestyle [9, 10].

Besides continuous medical care, diabetes requires continuous DSM behaviors and healthy lifestyles [11]. However, the effects of interventions aimed to improve the patients’ health-related behaviors are often inadequate and unsustainable [12]. One possible reason for this may be the failure to use social influences, such as social support, which are crucial for managing chronic conditions. Many studies have explored interventions based on family members’ participation, indicating that family members’ involvement in DSM is helpful to improve the patients’ glycemic control, knowledge related to diabetes, self-efficacy, and quality of life [13–18]. However, based on our literature review, very few studies in China have focused specifically on family members of diabetics [19, 20]. A multinational survey shows that only 25% of family members reported having attended diabetes programs [21]. Thus, the main obstacle to applying a chronic illness support model is the low participation rate of family members [22]. There may be several reasons for this lack of involvement. Family-based intervention usually consists of group sessions. Family members, especially young members, can hardly participate in programs requiring them to visit the appointed meeting place for long periods of time. Just as problematic are home visits, which are not sustainable and are hard to implement in daily practice, because health workers in health community centers already have heavy workloads [23].

The widespread use of smart phones in China, especially among the young, offers an opportunity to remove these obstacles in the implementation of family-based interventions. In China, WeChat is the most popular social networking platform, which is a free application characterized by high convenience and accessibility, presenting complex information by video and graphics, providing a feasible way to spread health information for the public [24]. Many studies show that WeChat has great potential in health intervention [25–29]. However, to our knowledge, few well-designed studies have focused on the combination of a WeChat-based intervention and the involvement of family members for those with type 2 diabetes mellitus in the community. This article is a study protocol for a randomized controlled trial for a family-based intervention via WeChat in two communities within urban China.

### Objectives

Our aim is to implement and evaluate a family-based intervention via WeChat for people with poorly controlled type 2 diabetes within an urban community.To examine the effectiveness of a family-based intervention via WeChat on clinical, psychosocial, and behavioral outcomes for patients with poorly controlled type 2 diabetes.To explore the feasibility and sustainability of this intervention and assess the process of participating in it.

## Methods

### Design and setting

A parallel, two-group, randomized controlled trial with equal allocation to the experimental group will be carried out over a year (Fig. 1). The participants will be randomly allocated to intervention group or control group. The participants in intervention group will receive the family-based intervention besides the usual care, while the participants in control group only receive usual care [8]. This study will be implemented and reported on the basis of Consolidated Standards of Reporting Trials (CONSORT) 2010 statement [30] and the Standard Protocol Items: Recommendations for Interventional Trials (SPIRIT) guidelines [31] (see Additional file 1).

**Fig. 1 Fig1:**
[figure not shown]
CONSORT flow diagram of the study design

The trial will be carried out in the central urban area of Jiading district in Shanghai, China. Jiading is located in the northwest of Shanghai. Per capita GDP of Shanghai in 2017 was 124,536 yuan, ranking it second among the 31 provinces in mainland China [32], while that of the whole mainland China was 59,660 yuan. The per capita GDP of Jiading in 2017 was 104,423 yuan, ranking it sixth among the 16 districts in Shanghai [33]. Nearly 150,000 residents live in this central urban area. Of them, 3873 are registered patients with type 2 diabetes according to the health information system of the basic public health services of the two health community centers in this area. Family doctor teams, usually consisting of one primary health doctor and 2–3 nurses, are responsible for providing the usual care stipulated by the national basic public health policy as their routine work. Diabetes self-management education (DSME), As an important part of usual care, is recommend to be held quarterly in the local community, consisting of basic diabetes information, how to practice self-monitoring of blood sugar, proper diet, how to inject insulin and other medications, physical activity, and foot care.

The blood glucose control compliance rate of registered diabetic patients from the two community health centers was 37.7% based on the available HbA1c data of 1650 patients in the health information system. This was close to the average rate in Shanghai city [34].

### Ethics and trial registration

The trial was ethically approved by Medical Research Ethics Committee at School of Public Health Fudan University (IRB#2018-01-0663), and the Trial Registration number is ChiCTR1900020736.

### Study participants

Both patients with poorly controlled type 2 diabetes and their designated family members will be participants in this study.

### Inclusion and exclusion criteria for patients

Inclusion criteria: 1) registered in the two community health service centers; 2) has had type 2 diabetes, diagnosed by a doctor at least 6 months before the study enrolment; 3) aged 18–79 years; 4) has HbA1c levels of ≥7.0%; 5) has no plans to leave home for the following 12 months; 6) has a family member who can use WeChat and lives with the patient or visits at least once a week.

Exclusion criteria: 1) has other serious illnesses or illnesses not suitable for this study; 2) women who are pregnant or preparing for pregnancy; 3) unable to complete 12-month follow-up; 4) unwilling or unable to provide informed consent; and 5) is currently participating in other intervention studies.

### Inclusion and exclusion criteria for family members

In this study we defined family members as relatives who contact with patients regularly. The family members will be nominated by patients. Patients need to choose one of his/her family members as a supporter to receive the corresponding intervention. The family member should be more than 18 years old and have no history of diabetes.

### Recruitment

The two community health centers consist of 12 community health service stations, with a family doctor team in each station. Twelve family doctor teams, responsible for the health management of people with type 2 diabetes in their routine work, will be recruited from the community health service stations. In this study, their tasks will include: mobilizing the participation of patients and their families and collecting baseline and follow-up data. After program training by researchers, they will commence the recruitment of potential participants.

Potential participants are those who have electronic medical records in the two community health centers. The family doctor team will call the patients with HbA1c data showing a value of ≥7.0%, explaining the objectives of the study and judging whether the patents are eligible to participate. In addition, due to the lack of HbA1c data for some patients in the database, the family doctor team will seek out potential eligible participants based on the data for fasting blood glucose during a patient’s last four follow-up visits that indicate poor glycemic control. The family doctor team will call the potentially eligible participants and explain the nature of the study. As part of eligibility assessment, all potential participants who are willing to participate will be asked to undergo HbA1c testing to make sure their HbA1c levels make them eligible.

Staff from the family doctor team will make an appointment for the eligible patients at the community health service station. At this appointment, patients and their family members can further consult project-related information. Once the patients and family members decided to participate, both will be asked to sign the consent form. Then, they will be asked to complete the baseline survey. The staff will keep a record the reasons for the eligible patients who reject to participate. In order to investigate sub-group differences, demographic variables, such as age and gender, will be compared between the participants and non-participants.

### Randomization

After collecting all baseline data, we will do the randomization at the individual level. Participants will be allocated to intervention or the control group in a 1:1 ratio. The randomization were performed by Stata 14.0 after all participants has been stratified by gender, duration of illness, and age. It is not possible to blind study researchers, the operator of the WeChat public account, or the participants due to the nature of the intervention. The community health service centers’ staff who are mainly responsible for collecting data, however, are blinded during the data collection.

All family members (not patients) from the intervention group will be invited to subscribe to the WeChat public account *Jiading Sugar Steward* on their smartphone (Fig. 2, the interface of this WeChat public account). This group will receive the usual care stipulated by the national basic public health policy. The controls will not be able to get access to the information of the WeChat public account.

**Fig. 2 Fig2:**
[figure not shown]
A sample interface of the Jiading Sugar Steward WeChat public account. Note: (**a**) The first module: information and skill; (**b**) Example content of the first module; (**c**) The second module: complications of diabetes; (**d**) The third module: lecture notice and a report about HbA1c value

### Intervention design

#### Conceptual model

A conceptual model for how family members’ knowledge about diabetes may influence patients’ health outcomes is presented in Fig. 3. The intervention was developed mainly on the basis of the Health Belief Model (HBM) [35], which is widely used for changing health-related behavior. The theory indicates that motivation toward preventive behaviors results from threat appraisal and the desire to avoid a potentially negative outcome [36].

**Fig. 3 Fig3:**
[figure not shown]
How family members may influence outcomes in diabetes

According to this model, education via WeChat will improve family members’ basic knowledge and skill. Therefore, they will have better ability to help the patients. In addition, they will have strong risk perception that patients with uncontrolled diabetes will suffer diabetes-related complications. As a result, both improved ability and risk perception will encourage and enable family members to take appropriate action in helping patients coping with diabetes. With the support of family members, patients may practice DSM with more confidence.

#### Information content

About 105 articles have been developed for the intervention based on *Guidelines for the Prevention and Treatment of Type 2 Diabetes in China-2017* [37]. A panel of five healthcare professionals of diabetes and/or patient health education will agree on the contents.

The article for this intervention will be divided into three main modules. The first module (Fig. 2a) consists of seven elements: 1) basic information about diabetes; 2) self-monitoring of blood sugar; 3) eating healthily; 4) insulin injections and medications; 5) reasonable exercise; 6) foot care; and 7) dealing with negative emotions. Information in this module covers basic knowledge about and the benefit of behavior change and how to practice it well. Common misunderstandings (Fig. 2b), such as that patients can stop medication when the blood sugar returns to normal, will be emphasized. Family members will be encouraged to help patients practice self-management behaviors and deal with negative emotions.

The second module (Fig. 2c) focuses on the possible complications of diabetes and dealing with emergencies like hypoglycemic coma and diabetic ketoacidosis. This information will give participants more details about the severity of diabetes and change the risk perceptions of family members.

The third module (Fig. 2d) is a news module consisting of two elements: a lecture notice and a report card containing the actual A1C value. The health education lecture notice will be released again in this module. We hope that the family member will encourage and remind the patients to attend all of the health education lectures. The report card will be presented with the patients’ current hemoglobin A1C and the ideal value. This report card will used as a form of feedback for family members to stimulate long-term social support.

#### Information delivery

To improve the accessibility of the intervention, the frequency and time of contacts must be considered. Too much information may bother participants. Thus, we decided to provide interventions twice a week. Although some studies have shown that WeChat users are more likely to receive push information from 8 a.m. to 11 a.m. and from 6 p.m. to 8 p.m. [38], there is no conclusion in terms of when is the most appropriate. Considering the working time of most people and the results of earlier studies [39], we will release the content at 5.00 p.m. to prompt the subscriber to accept the intervention. Due to the function of the WeChat application, the researcher can set the time to send the articles automatically. All information of this intervention can be conveyed by various methods such as text, images, videos, and audios.

#### Questions and quizzes

The participants will be encouraged to send their diabetes-related queries in the comments section after they have read the corresponding articles. The research staff, who are responsible for opening the public account, will collect queries every two days and send them to experts. Six experts (three from the Fudan University Zhongshan Hospital, two from the Jiading District Center for Disease Prevention and Control, one from Jiading Mental Health Center), as a consulting group, will address questions from participants.

In some important articles, quizzes will be included to improve the participants to actively read the articles and to assess how the participants master the information. The quizzes usually include 1–2 true-false or multiple choice items and is a closed test. To stimulate participants’ involvement, we will randomly select half of the quizzes and provide their takers with a monetary bonus. Participants who complete quizzes will get the bonus, usually 2–10 RMB, regardless of the correctness of the answer.

### Sample size

Sample size will be calculated based on the primary outcome, difference in mean HbA1c levels, assuming 80% power and a two-sided significance level of 0.05. The supposed effect size of HbA1c is 0.5%. We use the same standard deviation of HbA1C (1.2%) for calculations of the sample size, according to the data of 879 registered patients with HbA1C values more than 7.0% in the health information system in the two community health centers in central urban Jiading. Therefore, 92 participants are required in each group. Considering the possible lost follow-up rate of 20%, we will require 111 patients in each group for a total enrollment of 222 patient-family member dyads.

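### Enrolling 111 per group leaves 88 to 89 after the assumed 20% loss, not the 92 the plan says it needs

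*Protocol article*

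**What the plan says.** The Sample size section bases the calculation on the difference in mean HbA1c, "assuming 80% power and a two-sided significance level of 0.05". It takes a difference of 0.5 percentage points ("The supposed effect size of HbA1c is 0.5"%) and a common SD of 1.2 ("We use the same standard deviation of HbA1C (1.2%) for calculations of the sample size"), the latter from local records. The result is: "Therefore, 92 participants are required in each group". The next sentence applies the allowance for attrition: "Considering the possible lost follow-up rate of 20%, we will require 111 patients in each group", giving 222 patient-family dyads.

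The Randomization section confirms equal allocation: "Participants will be allocated to intervention or the control group in a 1:1 ratio". The Methods paragraph of the abstract repeats the total: "A total of 222 type 2 diabetics will be randomly divided into an intervention group or a control group". The article prints no formula for the allowance and gives no other loss rate or evaluable target.

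**The concern.** A loss to follow-up rate is a proportion of the people enrolled. To have n left when a fraction d is lost, one must enrol n / (1 − d). Multiplying n by (1 + d) is a common slip that always gives too small a number. Here the enrolment figure is exactly what the slip would produce, and it is below what the stated loss rate requires.

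At stake is the 80% power claim. The plan has almost no slack, because 92 is the smallest whole number that reaches 80% under its own inputs. The Discussion also says that web-based interventions of this kind face high dropout, so the loss allowance may well be tested in practice. That remark bears on whether 20% is a realistic rate. The arithmetic fault exists whatever the true rate turns out to be.

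**Working it through.** **Inputs** (Sample size section, with the ratio from Randomization): difference 0.5; SD 1.2 in both groups; two-sided alpha 0.05; power 80%; 1:1 allocation; loss 20%; stated results 92 evaluable and 111 enrolled per group.

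**Step 1: reproduce the 92.** The standardised difference is 0.5 / 1.2 = 0.4167.

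- Normal approximation: n = 2 × [1.2 × (1.960 + 0.842) / 0.5]² = 90.4, rounded up to 91.
- Two-sample t-test (noncentral t): n = 91.4, rounded up to 92. Power is 79.8% at 91 and 80.3% at 92.

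The stated 92 therefore reproduces with the t-test.

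**Step 2: apply the loss allowance.**

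- Dividing by the retained fraction: 92 / (1 − 0.20) = 92 / 0.8 = 115 per group, 230 in total.
- Multiplying by one plus the loss: 92 × 1.20 = 110.4, rounded up to 111 per group, 222 in total.

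The second matches the plan exactly and the first does not. That the plan multiplied is an inference, since no formula is printed.

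**Step 3: check 111 directly, however it was obtained.** 111 × 0.8 = 88.8, so 88 or 89 per group remain, 3 to 4 fewer than 92. The largest loss that still leaves 92 is 1 − 92 / 111 = 17.1%.

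**Step 4: power after 20% loss** (difference 0.5, SD 1.2, unadjusted comparison of those remaining):

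| Remaining per group | t-test | Normal approximation |
|---|---|---|
| 88 | 78.5% | 78.9% |
| 89 | 78.9% | 79.4% |
| 92 | 80.3% | 80.7% |

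**Step 5: does a different starting point rescue 111?** Starting from the normal-approximation figure of 91, the requirement is 91 / 0.8 = 113.75, rounded up to 114 per group (228 in total). The 88.8 remaining is still below 91. The shortfall shrinks from 4 to 3 per group but does not disappear.

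**The case against.** The strongest reply is that the error hardly matters.

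- **Size.** Power falls 1.1 to 1.5 points below 80%. With 88 to 89 per group, the difference detectable at 80% power is about 0.51 instead of 0.50, and an SD of about 1.18 instead of 1.2 would restore 80%. Uncertainty in the inputs is at least as large as the shortfall. This stands, and it is why the point is a correction to a stated figure and not a challenge to the design.
- **Planned analysis.** The Data analysis section specifies generalized linear mixed models for the longitudinal outcomes. Patients seen at 6 months but lost before 12 would still contribute, and baseline adjustment could add precision. The article gives no baseline to follow-up correlation. As an assumption, if the model adjusts for baseline, a correlation of about 0.2 would bring 88 per group back to 80%; 0.3 would give 82% and 0.5 would give 89%. It can also go the other way: an unadjusted change score with a correlation below 0.5 has less power than the table shows. This also stands as a limit on the power figures. It does not repair the sample size statement, which takes no credit for such gains and names 92 as the number required.
- **Mechanism.** Multiplication by 1.2 is not printed. That is so, but the finding does not depend on it, because 111 less 20% is below 92 by any route.

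**Conclusion.** The statement is wrong as written. A 20% loss rate, 92 evaluable per group and 111 enrolled per group are mutually inconsistent: at 20% loss the enrolment required is 115 per group, so the plan is short by 4 per group and 8 in total. Put the other way, 222 dyads cover 17.1% loss.

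The consequence is modest: power of about 79% at 20% loss instead of 80%. That figure assumes the plan's own difference and SD, equal loss in both groups, and an unadjusted two-sample comparison of those who remain. Power under the planned mixed model may be higher or lower and cannot be computed from what the article gives. The arithmetic inconsistency depends on none of these assumptions.

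**What to change.** Correct the sentence on loss in the Sample size section in one of two ways.

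1. **Keep 222** and state that 111 per group leaves the required 92 if loss does not exceed about 17%, or that at 20% loss it gives about 79% power for an unadjusted comparison. This costs nothing beyond a slightly less favourable power statement. The abstract needs no change, since it gives only the total of 222.
2. **Keep the 20% allowance and 80% power** and set the target to 115 per group, 230 in total, in both the Sample size section and the abstract. This costs 8 more dyads and is possible only if recruitment is still open.

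The Trial status section expected recruitment and baseline assessment to end in February 2019, and the Randomization section places allocation after all baseline data are collected. The first option is therefore likely to be the practical one.
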